## Abstract

**Introduction:** After a traumatic event, children and adolescents may present several clinical consequences, the most common being Post-Traumatic Stress Disorder (PTSD). Most children and adolescents with PTSD have comorbid disorders, such Attention Deficit Hyperactivity Disorder, depression, attachment and anxiety disorders, sleep disturbances and behavior problems. However, epidemiological studies on the development of PTSD and other psychiatric disorders in children and adolescents as a consequence of a terrorist attack and mass murder are lacking. Long-term follow-up of exposed children and adolescents will help identify risk and protective factors of developing psychiatric and psychological conditions after exposure to traumatic events or situations. The main objective of this article is to present the methodology of “14–7” program. The aim of “14–7” program is to characterize the risk and protective psychosocial factors affecting the clinical evolution of a pediatric population sample, exposed to the terrorist attack of July 14^th^, 2016 in Nice.

**Method and Analysis:** “14–7” program is a multicentre longitudinal cohort study. Major inclusion criteria are children and adolescents exposed to the terrorist attack and aged under 18 years on July 14^th^, 2016. These children and adolescents will be compared to a non-exposed to the “14–7” terrorist attack group, matched on age and gender. Participants will be assessed at baseline (T1), 2 years (T2) and 5 years (T3) after the initial assessment (T1), and every 5 years until they are 25 years old. Multiple domains are assessed: 1) mental health disorders, 2) intensity of PTSD symptoms, 3) intensity of comorbid symptoms, 4) quality of the parent–child relationship, 5) intelligence quotient, 6) parental symptoms. We will also establish a biological collection of saliva samples, magnetic resonance imaging (MRI) and actigraphy data collection. Main analyses comprise analyses of variance and regression analyses of predictors of clinical evolution over time.

**Ethics and Dissemination:** The National Ethics Committee “NORD OUEST III” approved the “14–7” Program protocol (number 2017-A02212-51). All patients and their caregivers signed informed consent on enrolment in the “14–7” Program. Inclusions started on November 21^st^, 2017. Three hundred thirty-five individuals have been included (191 children and adolescents, 144 parents).

**Clinical Trial Registration:**
www.ClinicalTrials.gov, identifier NCT03356028

## Background

On 14 July 2016 in Nice, celebration day in France, a terrorist attack happened. Many children and their families were impacted physically and psychologically. At least 30,000 people were present on the Promenade des Anglais (the attack site). This is the most important terrorist attack against families and children in France.

Eighty-six people died in the attack, including 10 children, the youngest being 4 years old. At least 55 children and adolescents were bereaved because of this crime. From 14^th^ 2016 to the beginning of the “14–7” Program (November 21^st^, 2017), 827 outpatients children, aged less than 18 years old, have consulted the child and adolescent psychiatry service as results of clinical consequences of this attack (1).

After being exposed to a traumatic event, children and adolescents may suffer from several clinical conditions (2). Among them, the most common is post-traumatic stress disorder (PTSD) (2). PTSD includes four main clinical symptoms: flashbacks of the event, avoidance behaviors, alteration of cognition and mood, and neurovegetative overactivation (3). Moreover, children and adolescents have specific clinical symptoms, such as general fears, developmental regression or traumatic re-enactment through play (4).

PTSD contributes to the development of many other mental disorders (5, 6). Around 75% of children and adolescents with PTSD have comorbid disorders. The main comorbidities identified in the pediatric populations are anxiety disorders, attention-deficit-hyperactivity disorder and depression (7, 8, 9). In addition, children and adolescents might present reactive attachment disorder, sleep disturbances and behavior problems (such as oppositional defiant disorder) (8).

Rates of PTSD in children and adolescents exposed to a potentially traumatic event have been shown to vary between 6% and 20% depending on several factors (10). That is, trauma history and exposure, sociodemographic, psychiatric, psychologic, environmental, and biological factors may modulate the development of PTSD.

Concerning psychological factors that have been found related to PTSD, the feeling of fear, during trauma and in the first month after the exposition to the traumatic event, is a risk factor implicated in the PTSD development (28). In a similar way, guilt and shame after the event predict the development of this disorder (29). Finally, cognitive alterations, that is, alterations of working memory and executive functioning and attentional biases are correlated with the occurrence and the risk of transition to PTSD chronic state symptoms (30).

Among environmental factors, family reactions during and after the trauma modulate the risk of PTSD development (31). Parental distress as well as parental PTSD and other parental mental disorders conduct to a higher risk of PTSD in children and adolescents (32, 33). On the contrary, quality of familial and social support, available psychological health care, recognition of traumatic impact by the society (31) have been identified as protective factors of PTSD development.

Finally, researches on adults have shown three biological markers of PTSD development: low cortisol 24 h after trauma (34), reduction of the volume of the hippocampus (35) and prefrontal dysfunction (36). Studies underlined that individuals with decreased hippocampus volume and prefrontal dysfunction following exposure displayed more PTSD-related symptoms 1 month after. In contrast, initial smaller hippocampus volume pre-exposure did not have an effect on PTSD-related symptoms (35).

Although several risk factors of PTSD in both children and adults have been documented, most research on risk factors of PTSD development in children and adolescents has focused on a small number of factors. Therefore, there is to date no integrative model of the PTSD development, and of risk of chronicity or relapse. Research on adult PTSD attempts to demonstrate the existence of different PTSD patterns consistent with symptoms, trauma and comorbidity (37) and to understand the temporal courses of PTSD (38). These results have not yet been replicated in children and adolescents.

Because both children and parents were exposed to the event and because of the nature of traumatic event, the prevalence of PTSD in the pediatric population implicated in the Nice attack may be very important.

The primary objective of the “14–7” Program is to characterize the risk and/or protective psychosocial factors affecting the clinical evolution of a pediatric population sample exposed to the terrorist attack of July 14^th^, 2016 in Nice.

Secondary objectives of the “14–7” Program are to examine efficacy of clinical treatments as a function of the developmental age of the child, and to develop recommendations for treatments and therapies.

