### Objectives

The main objective of “14–7” Program is to characterize the risk an*d/o*r protective psychosocial factors affecting the clinical evolution of a pediatric population sample, after the “14–7” terrorist attack.

Secondary objectives are: 1) assessment of the prevalence and incidence of mental health disorders, 2) assessment of the intensity of PTSD symptoms, 3) assessment of the intensity of comorbid symptoms, 4) assessment of the quality of the parent–child relationship, 5) assessment of the intelligence quotient, 6) assessment of parental symptoms 7) establishment of a biological collection of saliva samples, and 8) establishment of a magnetic resonance imaging (MRI) and actigraphy data collection.

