### Study Design

“14–7” is a longitudinal research involving human beings (i.e., French Law: category 2), with minimal risk and constraints, not involving health products. This search is a longitudinal follow-up study until participants reach the age of 25 years old. Participants will be assessed at baseline (T1), 2 years (T2), and 5 years (T3) after the initial assessment (T1), and every 5 years until they are 25 years old (**Figure 1**). During T1, T2, and T3 salivary samples will be taken from the included children and their parents, for all participants. At T1 and T2, actigraphy and MRI will be proposed for all participants.

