### Measures

Quantitative and qualitative measures are administered to the participants (summarized in **Table 1**):

Questionnaires regarding psychosocial risks (socio-demographic information; exposure to the traumatic event; care immediately after exposure; current care; social support, media exposure; legal procedure and assistance),Semi-structured interviews to assess the main diagnosis in children: MiniKid, Diagnostic Infant and Preschool Assessment (DIPA) or Kiddie—Schedule for Affective Disorders and Schizophrenia (K SADS),Salivary specimens for the construction of a biological DNA and RNA database,Clinical scales to assess PTSD: Young Child PTSD Checklist (YCPC), Child PTSD Checklist (CPC), or PTSD checklist (PCL),Clinical scales to assess anxiety: Preschool Anxiety Scale (PAS), Situational-Trait Anxiety Inventory for children (STAIC), or Situational-Trait Anxiety Inventory (STAI),Clinical scales to assess depression: Children’s Depression Rating Scale (CDRS) or Hamilton Depression Rating Scale (HDRS),Clinical scales to assess ADH/D (Conners),Clinical scales to assess dissociative experiences: Peri-traumatic Dissociation Experiences Questionnaire (PDEQ),Evaluation of social aspects: Brief Infant-Toddler Social and Emotional Assessment (BITSEA), Inventory of Parenting and Peer Attachment (IPPA), Kidscreen, parental stress index—short form (PSI-SF), or Post-Trauma Inventory of Parental Style (PIPS),Cognitive and socio-affective development for the youngest patients (Cognitive and Socio-Emotional Evaluation Battery: BECS) and intelligence quotient: Wechsler Preschool and Primary Scale of Intelligence (WPPSI), Wechsler Intelligence Scale for Children (WISC), or Wechsler Adult Intelligence Scale (WAIS).Parents’ clinical symptoms are also evaluated with the Clinical Global Impression (CGI), Clinical Global Assessment Scale (CGA), PCL, HDRS, STAI, PDEQ, PSI-SF and PIPS.

Clinical scales are all based on DSM-5 classification. They are scientifically validated assessment tools and are often used in clinical settings.

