### Outcomes

The main objective of “14–7” Program is to characterize the risk and/or protective psychosocial factors affecting the clinical evolution to the age of 25 years old of a pediatric population sample exposed to the mass trauma of 14 July 2016 in Nice.

Knowledge concerning risk and/or protective factors will help practitioners to detect children and adolescents at high risk of mental disorders in order to provide efficient follow-up and therapy.

Secondary objectives of the “14–7” Program are to examine efficacy of clinical treatments as a function of the developmental age of the child, and to develop recommendations for treatments and therapies. Results will therefore help future clinicians make evidence-based decisions on which treatment to use, depending on the developmental age of the child, and then help reduce the costs of trauma consequences.

Finally, in France, “14–7” Program should rapidly provide clinicians with adapted and standardized assessment tools validated in the pediatric population of all ages in the French language (e.g., DIPA, YCPC, CPC).

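### The secondary objectives conflict between sections, and the treatment-efficacy aim goes beyond what a cohort with unassigned care can establish

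*Protocol article*

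**What the plan says.** The protocol article states its secondary objectives in three places.

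- **Background (closing paragraphs):** the secondary objectives are to "examine efficacy of clinical treatments as a function of the developmental age of the child, and to develop recommendations for treatments and therapies".
- **Outcomes:** the same two aims are repeated, followed by the expectation "Results will therefore help future clinicians make evidence-based decisions on which treatment to use, depending on the developmental age of the child".
- **Objectives:** a different, numbered list opens "Secondary objectives are: 1) assessment of the prevalence and incidence of mental health disorders, 2) assessment of the intensity of PTSD symptoms" and runs to eight items. The others cover comorbid symptoms, the parent–child relationship, IQ, parental symptoms, saliva samples, and imaging with actigraphy. None concerns treatment.

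On design, Study Design describes longitudinal follow-up "with minimal risk and constraints, not involving health products". The comparison group is set out in the Abstract: "These children and adolescents will be compared to a non-exposed to the “14–7” terrorist attack group, matched on age and gender". Under Measures, care is one part of the psychosocial questionnaire: "care immediately after exposure; current care; social support, media exposure".

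**The concern.** Two things are wrong as written. First, the same label, secondary objectives, is attached to two lists that share no item. A reader cannot tell whether treatment efficacy is an objective of the programme.

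Second, if it is an objective, the word *efficacy* and the promise to guide treatment choice claim more than the design can give. Care was sought or received, not allocated. Children who received it are likely to differ in severity from those who did not, and that difference predicts later outcome. The Discussion says that guidance on type and duration of therapy is lacking, so a result labelled efficacy could be taken up as filling that gap. Limitations of the Study covers representativeness, avoidance, the time lapse and attrition, but does not mention that treatment is unassigned.

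**Working it through.** The plan gives no figure for a treatment effect, so there is none to reproduce. The check has two parts.

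**1. The sections side by side**

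- *Objectives.* Background and Outcomes agree with each other: efficacy by developmental age, and treatment recommendations. The Objectives section has eight items, none on treatment, and none of the eight is named as an objective in the other two sections. Each list reads as complete, so condensation of a longer protocol does not explain the difference.
- *Assignment.* Nothing in Study Design or Participants allocates treatment. Groups 1 and 2 are defined by exposure to the attack, so the matched controls answer a question about exposure, not about treatment.
- *Route into care.* The Background reports 827 outpatients under 18 who consulted child psychiatry because of clinical consequences of the attack. Participants names the hospital's consultation registry as a recruitment source. For these children, symptoms led to care.
- *Timing.* The attack was on 14 July 2016 and inclusions began on 21 November 2017, about 16 months later. Limitations of the Study concedes that the first year cannot be analysed prospectively. Early care, and the severity that prompted it, are known only in retrospect.
- *Sample size.* The calculation in Participants concerns PTSD frequency in exposed versus control children. It is not a basis for a treatment contrast or for a treatment-by-age contrast.

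**2. Could confounding by indication change the direction?**

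All inputs here are assumptions; the article gives none of them. Let p_t and p_u be the proportions with PTSD at T1 among treated and untreated children. Let PTSD persist to T2 in 40% with care and 60% without, so the true ratio among cases is 0.40/0.60 = 0.67 in favour of care. With no new onset and no adjustment:

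apparent ratio at T2 = (p_t × 0.40) / (p_u × 0.60) = 0.67 × (p_t / p_u)

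This exceeds 1, and so points against care, when p_t / p_u > 0.60/0.40 = 1.5.

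| PTSD at T1, treated / untreated | p_t / p_u | PTSD at T2, treated / untreated | Apparent ratio |
|---|---|---|---|
| 60% / 60% | 1.00 | 24% / 36% | 0.67 |
| 60% / 45% | 1.33 | 24% / 27% | 0.89 |
| 60% / 40% | 1.50 | 24% / 24% | 1.00 |
| 60% / 20% | 3.00 | 24% / 12% | 2.00 |

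Now add 5% new onset among children without PTSD at T1 to the last row. Treated: 0.24 + 0.40 × 0.05 = 0.26. Untreated: 0.12 + 0.80 × 0.05 = 0.16. The ratio is 0.26/0.16 = 1.6, still reversed.

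Under these assumptions the crude comparison therefore runs from unbiased, through attenuated, to reversed, depending on how much sicker treated children are at T1.

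**The case against.** The strongest reply is that this is loose wording in a condensed article. The primary objective is stated consistently in all three sections, the treatment sentences are forward-looking aims rather than results, and adjusted cohort associations can contribute evidence on treatment. All of that stands. It lowers the severity, but it does not reconcile the two lists or make unassigned care evidence of efficacy.

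Several stronger readings are tempting and are not supported:

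- *That the study is uncontrolled.* It is not. A non-exposed group matched on age and sex is planned. What is lacking is a control for treatment.
- *That the plan omits a treatment analysis.* A full protocol or SAP may contain one, so its absence from the article is no finding. The Background also counts available psychological care among environmental factors, and Statistical Analysis includes environmental variables among the predictors of clinical evolution, with analyses within the exposed group as well. The crude comparison in the table is not one that the article says it will run.
- *That care will look harmful, by a factor of two.* That is one assumed scenario. At 60% versus 45% there is no reversal.
- *That all care was given because of illness.* The article supports this for the outpatients who consulted. It does not say so for care given immediately after the attack.

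**Conclusion.** The point holds as a correction of stated aims. The secondary objectives in Background and Outcomes contradict those in Objectives. A comparison by care received in this cohort cannot establish efficacy, because care is unassigned, the controls are defined by exposure, the first year is retrospective, and symptoms led at least some children to care.

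The size of any bias cannot be derived from the article. Under the assumed persistence rates, with no new onset and no adjustment, the direction reverses only if PTSD at T1 is more than 1.5 times as common in treated children.

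A reader might infer that the study can say nothing about treatment. That goes too far: care is recorded, so adjusted associations by age can be estimated and can generate hypotheses. The primary objective, the sample size and the exposed-versus-control analyses are not affected. This should be corrected before any treatment result is reported, but it does not threaten the study's main purpose.

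**What to change.** 1. Reconcile the secondary objectives in Background, Objectives and Outcomes, so that one list appears throughout.
2. If treatment stays on the list, replace *efficacy* with an exploratory association between care received and later clinical course, by developmental age.
3. In Outcomes, restate the expectation of evidence-based treatment choice and recommendations as hypothesis-generating.
4. If an estimate is reported, make it within exposed children and relate care recorded at one wave to the outcome at a later wave. Always adjust for T1 symptom severity, diagnosis, age and the socio-demographic data collected. These covariates should not have to pass the bivariate p < 0.05 screen in Statistical Analysis, because a confounder can matter without passing it.

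Two limits should be stated with any such estimate. Measures names immediate and current care, so care between waves may not be fully recorded. It also names socio-demographic information without specifying socio-economic status. Adjustment reduces confounding by indication but cannot be assumed to remove it.

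The cost of items 1 to 3 is a few sentences and a more modest stated aim, with no change to data collection. Item 4 adds one exploratory analysis, which can be only as good as the care data recorded.

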## Methods/Design

### Ethical Consideration, Funding, and Registration

The “14–7” Program protocol was approved by the National Ethics Committee “NORD OUEST III” (number 2017-A02212-51).

All patients and their legal caregivers signed informed written consent upon enrolment in the study. The “14–7” Program has also been registered with ClinicalTrials.gov (number NCT03356028). Inclusions started on November 21^st^, 2017.

### Objectives

The main objective of “14–7” Program is to characterize the risk an*d/o*r protective psychosocial factors affecting the clinical evolution of a pediatric population sample, after the “14–7” terrorist attack.

Secondary objectives are: 1) assessment of the prevalence and incidence of mental health disorders, 2) assessment of the intensity of PTSD symptoms, 3) assessment of the intensity of comorbid symptoms, 4) assessment of the quality of the parent–child relationship, 5) assessment of the intelligence quotient, 6) assessment of parental symptoms 7) establishment of a biological collection of saliva samples, and 8) establishment of a magnetic resonance imaging (MRI) and actigraphy data collection.

### Study Design

“14–7” is a longitudinal research involving human beings (i.e., French Law: category 2), with minimal risk and constraints, not involving health products. This search is a longitudinal follow-up study until participants reach the age of 25 years old. Participants will be assessed at baseline (T1), 2 years (T2), and 5 years (T3) after the initial assessment (T1), and every 5 years until they are 25 years old (**Figure 1**). During T1, T2, and T3 salivary samples will be taken from the included children and their parents, for all participants. At T1 and T2, actigraphy and MRI will be proposed for all participants.

**Figure 1 f1:**
[figure not shown]
Study design and participants of “14–7” Program.

Each measurement occasion includes four visits. Measures administered at visits 1, 2, 3, and 4 are summarized in **Table 1**. Assessment will be performed by investigators [child and adolescent psychiatrists, (neuro)psychologists] specifically trained in psychotrauma and child psychiatry.

**Table 1 T1:** “14-7” Program procedure and evaluation criteria for the first study times.

		Selection	V1*	V2*	V3*
**Inclusion criteria**		X			
**Informed consent**		X			
**Psychosocial risks**			X		
**CGI/ CGA** (39, 4)			X		
**Salivary specimen**			X		
**DIPA** (40)	**Psychiatric evaluatio**n		X		
**MiniKid** (41)					
**K-SADS-PL** (42)					
**YCPC** (43)	**PTSD scale**			X	
**CPC** (44)					
**PCL** (45)					
**CDRS** (46)	**Depression scale**			X	
**HDRS** (47)					
**PAS** (48)	**Anxiety scale**			X	
**STAIC** (49)					
**STAI** (49)					
**BITSEA** (50)				X	
**PDEQ** (51)				X	
**Conners** (52)				X	
**IPPA** (53)				X	
**Kidscreen** (54)				X	
**PSI-SF** (55)				X	
**PIPS** (56)				X	
**BECS** (57)	**Cognitive and emotional evaluation**				X
**WPPSI** (58)					
**WISC** (59)					
**WAIS** (60)					

*V1, Visit 1; V2, Visit 2 and V3, Visit 3.

## Participants

Two groups were defined:

Group 1: children exposed to the “14–7” terrorist attack;Group 2: children non-exposed to the “14–7” terrorist attack.

Patient selection and recruitment:

Exposed children are recruited by consultation registry of the Nice CHU Lenval, ORSAN database (a national list of victims from terrorist attack). Controls will be matched on age and sex. Moreover, participants will be recruited *via* press advertisements and National Education. For the control group, categorical screening criteria were used to estimate the number of subjects necessary to reach a statistical power of 80% with a risk of type-I error (α) of 5% for the main outcome variable. Assuming a frequency of development of PTSD of 20% in the general population, to demonstrate a 40% increase in incidence (incidence rate found during violent and intentional traumatic events), it is necessary to include 1,122 participants; that is, 561 child controls. We will then include 600 children (150 per centre) matched on age and sex to the group of exposed children.

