### Inclusion Criteria

Exposed group:

Children, adolescents, and young adults of the Nice region exposed by the terrorist attack and aged under 18 years on July 14^th^, 2016, according to DSM 5.Children of pregnant women at the time of the Nice attack.Affiliated to a social security scheme;Fluent in French;Informed written consent of legal guardians and child/adolescent.

Non-exposed group:

Children, adolescents and young adults, matched in age and gender to exposed group;Non-exposed to the “14–7” terrorist attack;Affiliated to a social security schemeFluent in French;Informed written consent of legal guardians and child/adolescent.

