### Limitations of the Study

The main limitation of the “14–7” program might be the risk of non-representability of the entire pediatric population impacted by the terrorist attack.

First, individuals exposed to this attack and leaving outside the Nice region will be very difficult to be included. Second, children’ and/or parents’ avoidance behaviour might limit participation to the study. Third, the time lapse between the attack and the start of “14–7” Program does not permit to prospectively analyze clinical manifestations and PTSD during the first year. Nevertheless, questionnaires and diagnostic assessments include retrospective and lifetime evaluations. Finally, participant drop-out occurs in all prospective and longitudinal studies. Attrition not only causes loss of power because of diminishing numbers of participants, but if systematic, this may lead to selection biases and erroneous conclusions being drawn from a study. To prevent attrition, call phoning and newsletters are regularly realized for all participants.

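### Part of the exposed group comes from a consultation registry entered because of the attack's clinical consequences, so PTSD prevalence and the exposed-control difference risk overestimation

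*Protocol article*

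**What the plan says.** The Participants section gives two sources for exposed children: "Exposed children are recruited by consultation registry of the Nice CHU Lenval, ORSAN database", the second being described as a national list of victims. It adds that "participants will be recruited *via* press advertisements and National Education", without saying for which group. Controls are matched on age and sex; no clinical source is named for them.

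The Background says that 827 children under 18 "have consulted the child and adolescent psychiatry service as results of clinical consequences of this attack" between the attack and the start of the programme. It also says "At least 30,000 people were present on the Promenade des Anglais" (all ages; the number of children is not given).

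Eligibility for the exposed group has no symptom requirement: "Children, adolescents, and young adults of the Nice region exposed by the terrorist attack and aged under 18 years on July 14^th^, 2016".

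The first secondary objective is "assessment of the prevalence and incidence of mental health disorders". The Statistical Analysis section tests exposed against control by analysis of variance and runs analyses on the whole cohort and on the two groups. The sample size rests on the PTSD contrast between these groups.

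The limitations section concedes possible non-representativeness. Its reasons are residence outside the region, that "avoidance behaviour might limit participation to the study", the time lapse since the attack, and attrition.

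**The concern.** The eligibility criteria define the target as all exposed children of the region. One of the two named sources for that group is reached through a consultation. If, as the Background suggests, children consulted because of the consequences of the attack, then entry through this source depends on the outcome. An unexposed child cannot have consulted because of the attack, so the control group has no counterpart, and matching on age and sex does not supply one.

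Three results are exposed to this. Prevalence in the exposed group may come out higher than in exposed children at large. Part of the exposed-control difference may reflect the recruitment route. Associations within the exposed group may shift as well, because parental distress, support and available care, which the Background lists as risk or protective factors, plausibly also influence who consults.

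The limitations do not warn of this. Both recruitment problems they name, residence and avoidance, are forms of under-participation, and avoidance suggests a bias in the opposite direction.

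**Working it through.** **Inputs from the article.** Control PTSD rate 20%; a 40% increase, read as relative, so 20% × 1.4 = 28%; power 80%; alpha 5% (taken as two-sided); 1,122 participants, 561 per group.

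**The plan's own figure.** The pooled-variance formula for two proportions, 20% against 28%, gives 447 per group (894 in total), or 471 (942) with continuity correction. The stated 561 is not reproduced; it would give about 88% power. This point does not depend on the mismatch. The stated 561 is used below.

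**Inputs not in the article (assumed).** The share w of the exposed sample that comes from the registry, and the PTSD rate r among those children. The remaining exposed children are taken to have the true rate of 20%, so that the attack has no effect in this illustration.

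**Formulas.**
- Observed exposed rate: p = w × r + (1 − w) × 0.20.
- Rejection probability: Φ[(p − 0.20 − 1.96 × SE0) / SE1], where SE0 is the pooled and SE1 the unpooled standard error at 561 per group.

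**Worked case, w = 25%, r = 50%.**
- p = 0.25 × 0.50 + 0.75 × 0.20 = 0.275.
- Mean rate (0.20 + 0.275)/2 = 0.2375; SE0 = √(2 × 0.2375 × 0.7625 / 561) = 0.0254.
- SE1 = √((0.20 × 0.80 + 0.275 × 0.725) / 561) = 0.0253.
- (0.075 − 1.96 × 0.0254) / 0.0253 ≈ 1.00, so the rejection probability is about 84%.

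**Range.**

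| Registry share w | Registry rate r | Observed exposed rate | Rejection probability |
|---|---|---|---|
| any | 20% | 20.0% | nominal, no inflation |
| 15% | 30% | 21.5% | 9% |
| 15% | 40% | 23.0% | 23% |
| 25% | 40% | 25.0% | 52% |
| 25% | 50% | 27.5% | 84% |
| 50% | 40% | 30.0% | 97% |

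**Second model.** Let a child with PTSD be R times as likely to be in the registry as one without. The registry rate is then 0.20R / (0.20R + 0.80). For R = 2 this is 0.40/1.20 = 33.3%. With half the exposed sample from the registry, the observed rate is 0.5 × 33.3% + 0.5 × 20% = 26.7%, and rejection is about 75%. For R = 1.5 and a quarter from the registry, the observed rate is 21.8% and rejection about 11%. For R = 1 there is no inflation.

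Both models show that the result runs from negligible to nearly the whole planned 8-point difference. The article gives nothing that places the study within that range.

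**The case against.** The strongest objection is that neither the direction nor the size of a bias can be read from the article. The registry is one source among several. The victim list is not defined by symptoms, and press and school recruitment may bring in more exposed children, although the article does not say for which group. Avoidance could keep symptomatic children out. The Participants section does not call the registry psychiatric; that follows only from reading it with the Background. All of this stands. A reader might infer that prevalence and the group difference are inflated, or that a false positive is likely at 84%. The documents support neither: the 84% rests wholly on an assumed share and an assumed rate.

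Second, the limitations already concede non-representativeness and mention selection through attrition. This is true, but over-representation of care-seekers is not among the reasons given.

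Third, handling of recruitment source may sit in the full protocol or the analysis plan, and the Measures section already collects past and current care, social support and parental symptoms. Silence on source is therefore not itself the fault, nor does the article state that sources will be pooled without adjustment. What remains is what it does state: a source that depends on the outcome, a prevalence objective, and a comparison of the exposed group with controls.

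Fourth, the main objective concerns predictors of clinical evolution, and prevalence is one of eight secondary objectives. This limits the reach of the point, but the PTSD contrast still sizes the study.

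Finally, a reader might conclude that registry children should be left out of the main estimate. That can bias it downward. Assume a true exposed rate of 28% and 50% among consulters. If consulters are 25% of exposed children and all are removed, the rest have (0.28 − 0.125)/0.75 = 20.7%; if they are 10%, (0.28 − 0.05)/0.90 = 25.6%.

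**Conclusion.** The point holds as a risk of overestimation. Entry to part of the exposed sample depends on the outcome, the controls have no matching selection, and the limitations do not name the mechanism. Under the stated assumptions the effect of recruitment route alone runs from none, through an observed 23.0% with about 23% rejection, to 27.5% with about 84%, when the true rate is 20% in both groups. These figures show what is possible; they do not estimate what will happen. They rest on assumed registry shares and rates, on the other recruits having the true rate, and on 561 per group. Net direction stays open because avoidance may offset the bias, but nothing in the article shows that it would cancel it. Prevalence and the exposed-control contrast are mainly affected; distortion of the within-exposed associations is plausible but has not been quantified.

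**What to change.** - Record the recruitment source of each child (registry, victim list, press, school), allowing more than one, since the same child may be on the victim list and in the registry.
- Report prevalence and the exposed-control difference by source.
- Add a sensitivity analysis that excludes children reached only through the registry. Do not make it the primary set, because removing consulters can bias the estimate downward.
- Include source as a covariate in the within-exposed risk-factor models.
- Do not present the pooled figure as the prevalence in all exposed children.
- Name over-representation of care-seekers in the limitations, beside avoidance, and say that the two may act in opposite directions.
- State which group the press and school recruitment serves.

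The cost is one variable known at inclusion and some wording in the analysis plan. The downside is smaller strata and wider intervals for the source-specific estimates.
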